**Methods:**

The economic evaluation uses a within-trial analysis to evaluate the incremental costs and health outcomes of CONEMO plus enhanced usual care in comparison with enhanced usual care from public health care system and societal perspectives. Participants are patients of the public health care services for hypertension, diabetes, or both conditions in São Paulo, Brazil (n=880) and Lima, Peru (n=432). Clinical effectiveness will be measured by reduction in depressive symptoms and gains in health-related quality of life. We will conduct cost-effectiveness and cost-utility analyses, providing estimates of the cost per at least 50% reduction in 9-item Patient Health Questionnaire scores, and cost per quality-adjusted life year gained. The measurement of clinical effectiveness and resource use will take place over baseline, 3-month follow-up, and 6-month follow-up in the intervention and control groups. We will use a mixed costing methodology (ie, a combination of top–down and bottom–up approaches) considering 4 cost categories: intervention (CONEMO related) costs, health care costs, patient and family costs, and productivity costs. We will collect unit costs from the RCTs and national administrative databases. The multinational economic evaluations will be fully split analyses with a multicountry costing approach. We will calculate incremental cost-effectiveness ratios and present 95% CIs from nonparametric bootstrapping (1000 replicates). We will perform deterministic and probabilistic sensitivity analyses. Finally, we will present cost-effectiveness acceptability curves to compare a range of possible cost-effectiveness thresholds.

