## Methods

### Study Design

The economic evaluation will follow the Methodological Guidelines for Economic Evaluation Studies of Health Technologies [16] and will be reported according to the Consolidated Health Economic Evaluation Reporting Standards (CHEERS) checklist [17]. The multinational economic evaluations will be fully split analyses (incorporating estimates of both resource use and clinical effectiveness from the same group of patients from individual countries) with a multicountry costing approach (applying unit cost estimates from individual countries to account for resource use in each of those countries) [18]. The within-trial analyses will be conducted using data from the randomized control trials NCT02846662 and NCT03026426, and secondary data on health service costs extracted from governmental public databases. This protocol outlines the methods for a cost-effectiveness analysis and cost-utility analysis alongside the RCTs conducted in Brazil and Peru, respectively.

The proposed economic evaluations will be conducted from both the public health care system perspective (including only health care system costs) and the societal perspective (including health care system costs plus patient and productivity costs).

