### Time Horizon and Discount Rate

Time horizon analyses will use the study follow-up period: 3 and 6 months after the inclusion of participants in the study in order to understand its permanence effect. We truncated time horizons to the length of follow-up in the RCTs because the long-term health outcomes remain unclear and are not expected to last beyond 6 months.

Following the recommendations of the Methodological Guidelines for Economic Evaluation Studies of Health Technologies [16], we will not apply the standard discount rate of 5% on costs and benefits, because of the short (<1 year) time horizons.

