### Analytic Methods

Mean values of the estimated health outcomes and costs, as well as mean differences between the comparator groups (CONEMO plus enhanced usual care versus enhanced usual care) will be reported. Incremental cost-effectiveness ratios (ICERs) will be calculated as the arithmetic mean difference in cost between CONEMO plus enhanced usual care and enhanced usual care, divided by the arithmetic mean difference in effect. For the cost-effectiveness analysis, the corresponding ICER will be expressed as the incremental costs per at least 50% reduction of PHQ-9 scores. In the cost-utility analysis, the ICER will be expressed as the incremental costs per QALY gained. ICERs will be generated by nonparametric bootstrapping methods using random resamples for every 1000 pairs of outcomes and costs for the intervention and comparator groups to derive 95% CIs [27]. The distribution of mean incremental costs and outcomes shown on cost-effectiveness will be conducted to test the robustness of results.

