### Sensitivity Analyses

Deterministic and probabilistic sensitivity analyses will be performed to determine the level of confidence around the resulting ICERs. Several deterministic (1 way) sensitivity analyses will be carried out by varying the key parameters (such as quantity of resource use, unit cost of resource use, QALYs) in the within-trial analyses. Results from deterministic sensitivity analyses will be presented in a tornado diagram to compare the relative importance of the parameters with the ICER. The results from the probabilistic sensitivity analysis will also be presented using cost-effectiveness acceptability curves [28]. This curve indicates the probability that the CONEMO plus enhanced usual care is cost-effective compared with enhanced usual care, considering the thresholds range of $PPP3210-$PPP10,122 per QALY gained for Brazil, and of $PPP1969-$PPP7747 per QALY gained for Peru [29].

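### A 95% CI on bootstrapped ICERs is planned whatever the effect difference; if many replicates fall at or below zero effect, sorting them misorders dominated and dominant results

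*Protocol article*

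**What the plan says.** The Abstract (Methods) commits to the interval: "We will calculate incremental cost-effectiveness ratios and present 95% CIs from nonparametric bootstrapping (1000 replicates"). The Analytic Methods section defines the ICER as the mean cost difference "divided by the arithmetic mean difference in effect" and adds: "ICERs will be generated by nonparametric bootstrapping methods using random resamples for every 1000 pairs of outcomes and costs", from which the 95% CIs are derived. This covers both ratios, cost per patient with at least a 50% PHQ-9 reduction and cost per QALY. Study Design keeps the countries apart: "The multinational economic evaluations will be fully split analyses". So each ratio rests on one trial's sample, "in São Paulo, Brazil (n=880) and Lima, Peru (n=432").

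Neither section makes the interval depend on the effect difference, says how replicates with zero or negative effect are handled, or names the type of bootstrap interval. No interval for net benefit is mentioned.

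Three other outputs bear on the point. Analytic Methods also promises mean differences and a display of the joint distribution of incremental costs and outcomes (the sentence is incomplete; a cost-effectiveness plane is evidently meant). Sensitivity Analyses adds acceptability curves over a threshold range for each country, and a one-way display on the ratio: "Results from deterministic sensitivity analyses will be presented in a tornado diagram to compare the relative importance of the parameters with the ICER".

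**The concern.** A ratio jumps from plus to minus infinity as its denominator passes through zero. Once replicates lie on both sides of zero effect, their ICERs have no meaningful order. Dominant replicates (cheaper, better) and dominated ones (dearer, worse) both come out negative. If the intervention costs more on average, most negative ratios are dominated replicates, and sorting puts them at the end that looks most favourable. A reader would take a negative lower limit as possible cost saving when the replicates behind it show the opposite.

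The cost-per-QALY ratio is the more exposed of the two. The analysis looks at "3 and 6 months after the inclusion of participants in the study" and goes no further: "We truncated time horizons to the length of follow-up in the RCTs". A utility gain therefore has at most half a year in which to become QALYs, and the split by country rules out pooling to sharpen the difference.

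**Working it through.** The protocol gives no expected ICER, QALY difference or SD, so there is no figure to reproduce. The check asks how small the effect must be for the problem to arise.

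**Inputs from the protocol:** 880 participants in Brazil and 432 in Peru; horizon of at most 6 months; 1000 replicates; thresholds of $PPP 3210–10,122 (Brazil) and 1969–7747 (Peru) per QALY.

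**Assumptions, not in the protocol:** 1:1 allocation (440 and 216 per arm), no loss to follow-up, 6-month QALY SD 0.06–0.12. For the worked example: QALY SD 0.10, cost difference 60, cost SD 300.

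**Step 1. Utility gain to QALYs.** With equal baselines and a gain g at 3 and 6 months, the area between the curves is dQ = 0.5 × 0.25 × g + 0.25 × g = 0.375g.

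**Step 2. Share of negative replicates.** This is Φ(−dQ/SE), with SE = SD × √(2/n per arm). √(2/440) = 0.0674 and √(2/216) = 0.0962. It stays below 2.5% only if dQ exceeds 1.96 × SE.

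| Country | QALY SD | SE | dQ needed | g needed (dQ/0.375) | Negative share at g = 0.02 (dQ = 0.0075) |
|---|---|---|---|---|---|
| Brazil | 0.06 | 0.0040 | 0.008 | 0.021 | 3.2% |
| Brazil | 0.10 | 0.0067 | 0.013 | 0.035 | 13.3% |
| Brazil | 0.12 | 0.0081 | 0.016 | 0.042 | 17.7% |
| Peru | 0.06 | 0.0058 | 0.011 | 0.030 | 9.7% |
| Peru | 0.10 | 0.0096 | 0.019 | 0.050 | 21.8% |
| Peru | 0.12 | 0.0115 | 0.023 | 0.060 | 25.8% |

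Bootstrap replicates centre on the observed difference. If the true gain sits exactly at the limit, about half of such trials would still observe less: Φ(1.96 − 1.96) = 0.5.

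**Step 3. What the interval would look like.** A nonparametric bootstrap was run on one constructed data set per country, with dQ = 0.0075 and an ICER of 60/0.0075 = 8000.

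- Brazil: 13.1% of replicates had negative effect. The 2.5th and 97.5th percentiles were −104,187 and 74,234. Dominated 13.0%, dominant 0.2%.
- Peru: 20.2% negative. Percentiles −63,174 and 96,713. Dominated 19.7%, dominant 2.2%.

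The negative end is thus almost wholly made of dominated replicates. Since dQ/SE is 0.0075/0.0067 = 1.11 (Brazil) and 0.0075/0.0096 = 0.78 (Peru), both below 1.96, the Fieller set is unbounded and no finite interval is right for these data.

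**Step 4. Coverage of the percentile interval** (simulated). At dQ of 0.0075–0.01875 it is 96–98%. At 0.00375 it is about 95–96% (Brazil) and 93–94% (Peru). It drops clearly only near zero effect: 82–92% at 0.002 and roughly 54–82% at 0.001, depending on country and SDs. Practically all misses are on the high side.

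**Step 5. Responder ratio.** For an assumed 28% v 38%, SE = √[(0.28×0.72 + 0.38×0.62)/n per arm] = 0.0315 (Brazil) and 0.0450 (Peru), so 0.1% and 1.3% of replicates are negative. For 28% v 33% the shares are 5.3% and 12.9%.

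**Step 6. Net benefit on the same example.** INMB = λ × dQ − cost difference. For Brazil at λ = 3210: 24.1 − 60 = −36, SE = √[(3210 × 0.00674)² + (300 × 0.0674)²] = 29.6, 95% CI −94 to 22. At λ = 10,122: 16 (−124 to 155). For Peru at 1969: −45 (−113 to 22); at 7747: −2 (−159 to 155). These limits are ordered and can be read directly. In the coverage simulations, the net-benefit interval evaluated at the true ICER held 94–96% in every scenario.

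**The case against.** Four objections carry weight.

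- The protocol does not name a percentile interval. It cites a source for the bootstrap, and a condensed article may leave the construction to a fuller plan. That stands as to type. But both places commit to an ICER interval without condition, and any interval built by sorting bootstrapped ICERs has the ordering problem, so leaving the type open does not remove it.
- The plan already includes mean differences, the joint distribution and acceptability curves. The last two stay valid across quadrants and would show a careful reader the dominated replicates. This softens the consequence. It does not replace the interval that will be printed beside each ICER.
- The small QALY difference is an assumption. This is right, and it is why the size is given as a range. In Brazil, a sustained utility gain of 0.05 at SD 0.10 leaves 0.3% negative replicates and no practical problem.
- The tornado diagram is mostly sound. A parameter that moves only costs leaves the denominator fixed, so the ICER moves linearly and stays ordered. Only a bar that takes the effect through or near zero, such as QALYs, is affected.

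A reader might also infer that the interval undercovers in general, or that every ICER in the study is affected. Steps 4 and 5 show neither. Nor is zero coverage under a true null effect evidence against the method: with a positive cost difference the true ratio is then infinite, and no finite interval could contain it.

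**Conclusion.** The point holds as a conditional one. The plan fixes a 95% CI on bootstrapped ICERs whatever the effect difference, and this misleads when a material share of replicates is at or below zero effect. The harm is misordering and misreading; real undercoverage appears only very close to zero effect.

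Assuming a 6-month QALY SD of 0.06–0.12, 1:1 allocation and no loss, the cost-per-QALY interval is affected when the gain is below about 0.008–0.016 QALY in Brazil or 0.011–0.023 in Peru. That corresponds to a sustained utility gain of roughly 0.02–0.04 or 0.03–0.06. The cost-per-responder interval is affected only for a small responder difference, around 5 points in the example. With a clear effect the planned interval is adequate.

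This is a moderate flaw in one reported interval, not a failure of the whole uncertainty analysis. It should be corrected before the analysis is run.

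**What to change.** Keep the ICER as a point estimate and state its quadrant. Keep the joint distribution, naming the cost-effectiveness plane in the incomplete sentence, and the acceptability curves. From the same 1000 replicates, report:

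- 95% CIs for incremental cost and incremental effect, for both outcomes;
- for QALYs, incremental net monetary benefit with a 95% CI at the lower and upper threshold already listed for each country.

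Give an ICER interval, and name its type, only if the replicates lie clearly on one side of zero effect (for example, fewer than 2.5% on the other side). Otherwise report the share of replicates in each quadrant or a Fieller set. In the tornado diagram, use net monetary benefit for any parameter whose range takes the effect through or near zero.

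The cost is a few sentences in the analysis plan and a few lines of code. No new data or resampling is needed.

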### Sensitivity Analyses

Deterministic and probabilistic sensitivity analyses will be performed to determine the level of confidence around the resulting ICERs. Several deterministic (1 way) sensitivity analyses will be carried out by varying the key parameters (such as quantity of resource use, unit cost of resource use, QALYs) in the within-trial analyses. Results from deterministic sensitivity analyses will be presented in a tornado diagram to compare the relative importance of the parameters with the ICER. The results from the probabilistic sensitivity analysis will also be presented using cost-effectiveness acceptability curves [28]. This curve indicates the probability that the CONEMO plus enhanced usual care is cost-effective compared with enhanced usual care, considering the thresholds range of $PPP3210-$PPP10,122 per QALY gained for Brazil, and of $PPP1969-$PPP7747 per QALY gained for Peru [29].

### Statistical Software Use for Health Economic Analysis

Stata (StataCorp) version 15.0 or higher will be used for all health economics analyses.

## Results

Phase 1 of the project ran from September 2016 to April 2018 to assess the applicability of CONEMO. Phase 2 began in June 2018 and is expected to be completed in September 2021. The economic evaluation of CONEMO will be conducted during this phase. Results will be used to report the costs of CONEMO to help plan the implementation of the intervention. The evaluation will also calculate the cost-effectiveness of CONEMO to improve symptoms of depression.

## Discussion

### Overview

Assessing the economic viability of the CONEMO intervention based on its cost-effectiveness will enable us to ascertain the feasibility of its implementation in primary and secondary care. If shown to be financially viable, the intervention could help bridge the treatment gap and increase access to mental health care. If the ICER is favorable, there would be a strong case for policymakers to support the scale-up of this intervention.

Implementing the CONEMO intervention would enable the screening, identification, and treatment of depression in patients with chronic diseases. The expected result is a reduction in symptoms and likely an increase in self-care, adherence to treatment, and quality of life. These outcomes could also result in fewer complications and required resources, as well as reduced health care costs. Using nursing staff to support patients rather than specialized mental health professionals and specialized services could also be an efficient use of human resources, thereby saving costs in the longer term.

Economic evaluations are particularly important because they can be used to guide decision makers or funders in determining if the mHealth interventions improve health outcomes when compared to other existing interventions [15]. They are also important for analyzing whether the cost to adopt and maintain the intervention in a health system is justified. One of the barriers of mHealth implementation and scale-up is the financial feasibility, yet few studies include or detail operational costs of mobile communication, such as fees charged to end users (patients).

### Generalizability and Future Research

If found to be clinically effective and cost-effective, CONEMO could be used in other populations with similar treatment gaps [13]. Replication has been made possible by the standardized materials used. The generalizability of results is likely high due to the diverse in-country heterogeneous sample and its implementation in 2 countries.

Implications for health provision and use: We would seek to collaborate with other services to develop further evidence for implementation.Implications for health policies: Despite some limitations, this protocol will be used to measure the costs of mental health services in 2 studies, generating data to support local mental health policies, boost research in the country, and support new studies.

### Study Limitations

Health economic evaluation studies on mHealth interventions have not been conducted in Brazil and Peru; while this is an innovative research study, some limitations remain. These are as follows:

Cost-effectiveness analysis may be hampered by the scarcity of economic and epidemiological data available and the composition of the variables for each cost when found.Peruvian analysis will follow Brazilian guidelines due to the lack of guidelines for health economic evaluation in Peru.Some cost items will be based on other similar items, which do not express the same precision level of a specialized service sample collected on official cost indicator databases.Difficulty in including all indirect costs incurred from the societal perspective due to insufficient information related to the treatments under analysis.

## Abbreviations

CONEMO: control emotional (emotional control intervention)
DATASUS: Departamento de Informática do Sistema Único de Saúde (Department of Informatics of the National Health System)
EQ-5D-3L: EuroQol 5-dimensional questionnaire, 3-level version
FFAA: Fuerzas Armadas
ICER: incremental cost-effectiveness ratio
LATIN-MH: Latin America Treatment and Innovation Network in Mental Health
LMIC: low- and middle-income countries
mHealth: mobile health
NA: nurse assistant
PHQ-9: 9-item Patient Health Questionnaire
PPP: purchasing power parity
QALY: quality-adjusted life year
RCT: randomized controlled trial
SIS: Seguro Integral de Salud (Integral Health Insurance)
